## 1. Background

According to estimates, 15 million premature births occur every year worldwide. China has the second largest number of premature infants in the world, 1.17 million premature births are reported in China every year, accounting for 10% of all newborns. Delayed action of full enteral nutrition in preterm infants is closely associated with an increase in morbidity and mortality. Delayed meconium evacuation is a recognized cause of intestinal dysfunction, which can cause delayed feeding, gastric retention, and feeding intolerance in preterm infants. The immature intestinal motility mechanism and neurotransmitter system of low-birth-weight infants delay meconium evacuation. Moreover, viscous meconium causes functional blockage of the intestines and abnormal gastrointestinal functions. The younger the gestational age of premature infants, the later and longer the meconium evacuation. Studies have shown that early meconium evacuation improves feeding intolerance and promotes weight gain. Because the meconium contains high levels of bilirubin, a delay in meconium evacuation increases the intestinal circulation of bilirubin, thereby aggravating neonatal jaundice and increasing the risk of bilirubin brain damage, kernicterus, serious sequelae, and even death.

Currently, the widely used strategies for inducing meconium evacuation worldwide are glass rod stimulation of the rectum, enema with formulations and oral intake of glucosamine (Gastrografin). Among them, enemas are the most commonly used approach. The formulations used for enemas include solutions (including physiological saline, glycerin, and diatrizoate) and suppositories (mainly glycerin). Glucosamine, a formulation for meconium evacuation that has emerged in recent years, is a gastrointestinal contrast agent that can be administered orally or rectally and has a hyperosmotic effect. However, the effects of glucosamine in meconium evacuation remain controversial. Glycerin solutions and glycerol suppositories have been widely used abroad as enema formulations, although a meta-analysis has suggested that the effects of glycerol solutions or glycerol suppositories in preterm

infants are unclear. Saline is the most widely used formulation, but a systematic review has shown that saline does not shorten the total feeding time of preterm infants.

Because the effects of the above commonly used enema formulations are controversial, identifying a new enema formulation is necessary to increase meconium evacuation in premature infants. Studies have shown that breast milk has appropriate osmotic pressure and high safety in stimulating the digestive tract in infants. Therefore, we aimed to explore whether a breast milk based enema might shorten the time of the last meconium evacuation and the time to achieve full enteral feeding in super premature infants and preterm infants.

## **2. Objectives**

(1) Explore whether breast milk can shorten the time of the last meconium evacuation in super premature infants and preterm infants.

(2) Explore whether breast milk can shorten the time of full enteral feeding in super premature infants and preterm infants.

(3) Evaluate whether breast milk can decrease the enterohepatic circulation of bilirubin and the incidence of cholestasis in super premature infants and preterm infants.

## **3. Study design and organization**

### **3.1 Overview of the study design**

We aim to explore whether breast milk might shorten the time of the last meconium evacuation and the time of achieve full enteral feeding in super premature and preterm infants. Saline will be used as a control. We will use a randomized controlled trial to recruit eligible subjects and assign them to intervention and control groups. The control group will receive saline, and the intervention group will receive breast milk for meconium evacuation (**Figure 1**).

[figure not shown]

**Figure 1. Flow chart of study design.**

## 3.2 Study organization

**Figure 2** shows the study organization.

[figure not shown]

**Figure 2. Study organization.**

### 3.2.1 Study steering committee

This trial will be supervised by the study steering committee, which will consist of experts in epidemiology, pediatrics, and infectious disease. The committee will oversee the study design, implementation, data analysis, and reporting of the trial. The main responsibilities of the committee will include the execution of research programs, personnel training, supervision, and guidance.

### **3.2.2 Study and data coordination center**

The study and data coordination center is located at Shengjing Hospital of China Medical University. The study and data coordination center will work closely with the study steering committee to provide scientific and administrative support for the trial. The main responsibilities of the study and data coordination center will include implementation of the randomization process, data quality control, preparation of reports, and data analysis for the study steering committee and the data safety monitoring committee. In addition, it will meet weekly to communicate issues and perform troubleshooting.

### **3.2.3 Data safety monitoring committee**

The data safety monitoring committee will monitor any safety issues that occur during the trial, and will conduct monitoring and recording and propose solutions.

## **4. Study population**

### **4.1 Recruiting criteria**

In this project, we will recruit super premature infants and preterm infants at the Department of Neonatology, Shengjing Hospital of China Medical University as eligible subjects. The inclusion and exclusion criteria for the study participants will be as follows:

Inclusion criteria:

(1) Super premature infants  $23W \leq \text{gestational age} < 28W$

Preterm infants  $28W \leq \text{gestational age} < 30W$

(2) Mother provides breast milk 48 hours after birth.

(3) Normal intestinal motility (as assessed by the team of clinical experts)

165 (4) Parental agreement to participate in the study

166 Exclusion criteria:

167 Premature infants meeting any of the following table will be excluded.

| Criteria                              | Definition                                                                                                                                                                                                                                                                             |
|---------------------------------------|----------------------------------------------------------------------------------------------------------------------------------------------------------------------------------------------------------------------------------------------------------------------------------------|
| Congenital malformations              | Congenital malformations are structural or chromosomal malformations that have a major impact on health and development.                                                                                                                                                               |
| Congenital gastrointestinal anomalies | Congenital gastrointestinal anomalies are mainly diagnosed by ultrasonography or radiography. Congenital gastrointestinal anomalies include gastric volvulus, cecal volvulus and heterotopic pancreas, etc.                                                                            |
| Anorectal deformities                 | Anorectal deformities are a wide spectrum of abnormalities of the anus and rectum, which include anal atresia, rectovesical fistula, etc. Anorectal deformities will be diagnosed by Magnetic resonance or sonography.                                                                 |
| Diarrhea                              | Diarrhoea is defined as the occurrence of 3 or more loose stools within 24h.                                                                                                                                                                                                           |
| Intussusception                       | Intussusception is characterized by telescoping of one part of the gastrointestinal tract into another part, forming an obstruction. Intussusception will be diagnosed by ultrasound.                                                                                                  |
| NEC                                   | The main symptoms of NEC are abdominal distension and hematochezia, which are characterized by intestinal mucosal necrosis. NEC is mainly diagnosed by abdominal X-ray and ultrasound examination.                                                                                     |
| PDA                                   | PDA will be confirmed by echocardiography                                                                                                                                                                                                                                              |
| Sepsis                                | Sepsis includes early-onset and late-onset. Early-onset sepsis is caused by pathogens transmitted from mothers, and late-onset sepsis is caused by nosocomial infections. Sepsis is defined as the overgrowth of bacteria in blood cultures in the presence of clinical deterioration. |
| Neutropenia                           | Absolute neutrophil count $<0.5 \times 10^9/L$                                                                                                                                                                                                                                         |
| Coagulopathy                          | International standardization ratio $>1.4$ , Partial thromboplastin time $>39s$ , Fibrinogen $<1.00g/L$ , Platelet count $<100 \times 10^9/L$                                                                                                                                          |

168

169 Necrotizing enterocolitis: NEC ; Patent ductus arteriosus: PDA.

170 **4.2 Recruitment**

We propose to recruit 78 super premature infants and 216 preterm infants from the Department of Neonatology, Shengjing Hospital of China Medical University. Recruitment will occur from June 2019 to September 2020 and will be conducted on-site. Leaflets with trial information will be displayed onsite in the waiting room of the neonatology department. A research assistant will ask each participant's guardian if they would be interested in having their babies participate and will be given sufficient time to make their decision. The guardian can contact the research assistant using the provided telephone number and undergo screening to enter the trial.

#### **4.3 Informed consent**

If the guardian is willing and the infant is eligible to participate in the study, the participant's guardian will be required to sign a written informed consent. Informed consent procedures will ensure that participant's guardian understands participation is voluntary and that participants can withdraw from the study at any time. The informed consent can be obtained from the corresponding author.

#### **4.4 Additional consent provisions**

The main trial consent asks mothers of participants if they would be willing to allow the use of their baby's data if they choose to withdraw from the trial. This trial does not involve collecting biological specimens for storage.

### **5. Randomization**

Participants will be allocated to intervention and control groups with stratified block randomization using a computer-generated randomization list by an independent statistician not otherwise involved in the trial. The participants will be stratified based on gestational age. Then, the participants will be assigned in a randomized block design to the intervention and control groups in a 1:1 ratio. Block size will be 4 and 6 to ensure equal numbers of participants in the intervention and control groups. At the beginning of the trial, random sequence will generate a set of study numbers. Each study number will be paired with a method of intervention and sealed in an opaque envelope. The envelopes will be grouped based on gestational age. Recruited

participants will be allocated to intervention or control groups by selecting an envelope. The program will be set up using SAS 9.2 (SAS Institute Inc., Cary, NC).

## **6. Blinding**

The design is open-label with only outcome assessors and data analysts being blinded to decrease bias and increase the accuracy of data collection.

## **7. Intervention**

### **7.1 Intervention scheme**

Preterm infants in control and intervention groups will receive a saline and breast milk enema, respectively. Nurses will be trained to ensure the standardized and safe administration of enemas. The timeline of the trial is shown in Figure 2. The specific procedures are described as follows:

(1) Meconium evacuation procedure: preterm infants in intervention and control groups will undergo meconium evacuation twice per day at 9:00 and 21:00. The intervention will continue until the meconium is completely evacuated.

(2) Preparation of materials: silicone tube (4–6 cm, model 3.33 mm [F10]), 5 mL syringe, thermostat (temperature setting 37°C), sesame oil, sterile gloves.

(3) Implementation: The number of enemas required will be calculated (5 mL/kg) and preheated to 37°C in a thermostatically controlled water bath. The preheated enemas will be extracted with a syringe. One end of the silicone tube will be connected to the syringe and the other end will be lubricated with sesame oil before inserting it 2–3 cm into the rectum. The enema will be slowly injected into the rectum and will be retained there for 3 minutes; the silicone tube will then slowly be pulled out.

If a premature infant does not pass stools during the 24 hours following the complete evacuation of meconium, an enema will be administered. A saline enema will be used once a day in both intervention and control groups using the same method as described above.

Criteria for the termination of intervention will include complete meconium evacuation, the development of any of the serious adverse events listed in the outcomes below or the withdrawal of a guardian's consent.

To improve adherence and promote participant retention, nurses and doctors will be trained in study-specific procedures prior to participation in the study. In addition, guardians will be updated weekly on the status of their infants by a nurse who is otherwise not involved in the study. The Trial Steering Committee (TSC) will also dynamically monitor the rate of follow-up loss.

## **7.2 Feeding schedule**

The same feeding and parenteral nutrition procedures will be used for premature infants in control and intervention groups. The total daily calories of enteral and parenteral nutrition will be 110–135 kcal/kg. Premature infants will be fed starting at 24 mL/kg birthweight per day. Furthermore, feedings will be advanced every 24 hours by 20 mL/kg birthweight per day. When the amount of enteral feeding reaches 120 mL/kg per day, parenteral nutrition will be stopped. We defined full enteral feeding as tolerance of enteral feeding volumes of 180 mL/kg/day within 24 hours and a weight gain greater than 20–25 g/d within 24 hours. Human milk feeding will be encouraged. If the amount of breast milk is insufficient to meet the nutritional needs of premature infants, mixed feeding (artificial and breast milks) will be adopted. We will use disposable bottles for feeding to calculate the volume of feeding and use nasogastric feeding for premature babies with poor sucking ability. Feeding will be stopped if feeding intolerance occurs, such as when a gastric residual volume occurs that is more than half of the feeding volume, an abdominal circumference that is increased by 2 cm more than before the previous feeding, or with the occurrence of an intestinal dynamic anomaly.

## **7.3 Study termination**

The study will be terminated in the event of sepsis, NEC, fecal occult blood positive, diarrhea, or rectal or anal injury.

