### **8.2 Secondary end-points**

(1) Stage II or III necrotizing enterocolitis (NEC, Bell standard)

(2) Hospitalization days

(3) Body weight at discharge

(4) Duration of total parenteral nutrition

(5) Cholestasis(Serum binding bilirubin concentration > 1.0 mg/dL (17.1 mmol/L)

Serum total bilirubin < 5.0 mg/dL (85.5 mmol/L) or >20%

Total bilirubin concentration >5.0 mg/dL (85.5 mmol/L), measured 2 weeks after birth in two groups

(6) Any adverse events reported: nosocomial infection, nosocomial death, retinopathy of prematurity (ROP, any stage), chronic lung disease (CLD), requirement of ventilatory support or oxygen after a corrected gestational age of 36 weeks, intraventricular hemorrhage (IVH, grade 2 and above), bronchopulmonary dysplasia (BPD), late-onset sepsis (LOS), diarrhea, colon perforation, malabsorption, rectal bleeding, and rectal trauma.

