## **9.2 Follow-up data collection**

(1) End-point information: body weight (g), meconium evacuation time (h), fecal type, abnormal traits and color; time to achieve total enteral feeding (h), duration of total parenteral nutrition (h), feeding tolerance (residual milk volume, nature of the residual liquid, abdominal circumference before the two feedings, bowel sounds, and intestinal motility conditions), route and method (breast milk only/breast milk formula mixed/formula milk powder only) of feeding, type of formula, C-reactive protein measurements, blood culture results, blood oxygen measurements, Whether to perform phototherapy, serum bilirubin levels, neonatal intensive care unit time, and NEC.

(2) Adverse events: nosocomial infection, in-hospital death, ROP, CLD, IVH, BPD, LOS, diarrhea, colon perforation, malabsorption, rectal bleeding, and rectal trauma.

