### **10.3 Missing data**

The relevant researcher will contact the premature infant's guardian by telephone or check electronic medical records to supplement missing baseline and follow-up data. If no reply is received from the guardian or missing data cannot be supplied, the missing data will be processed using different methods based on the mechanism of the missing data. For example, mean value imputation and last observation carried forward will be used to supplement the data. Furthermore, we will conduct a sensitivity analysis to evaluate the robustness of trial results: When we analyze primary outcomes, we will conduct a comparative analysis of complete (ignoring the missing data) and incomplete (no missing data) cases.

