### **12.3 Frequency and plans for auditing trial conduct**

The Trial Management Team will meet every 3 months to review the implementation of the study. The independent monitor will make an on-site visit once a month and check the quality of the data, including inclusion and exclusion criteria, informed consent, original data, and the absence of data.

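### Section 7.3 ends the study, not just the enemas, so read with 12.8 it lets follow-up stop before full enteral feeding is observed in an infant who meets a 7.3 trigger

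*Protocol*

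**What the plan says.** Two sections govern stopping.

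- **Section 7.1** concerns the intervention only. Enemas end when meconium is fully evacuated, when a guardian withdraws consent, or on "the development of any of the serious adverse events listed in the outcomes below".
- **Section 7.3**, headed as study termination, reads: "The study will be terminated in the event of sepsis, NEC, fecal occult blood positive, diarrhea, or rectal or anal injury". It does not say whether this means the enemas, the infant's participation or the trial.

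The length of follow-up is set in **section 12.8**: infants are followed daily until the endpoints are reached or until termination of the trial is required. No other section says how long an infant is followed after an event.

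The endpoints at issue are time to full enteral feeding, the second primary endpoint in section 8.1, and hospital days and discharge weight in section 8.2. Section 14.1 commits to intention-to-treat and per-protocol analyses.

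**The concern.** Staff at the bedside have to decide what stops when an infant develops, say, sepsis. Section 7.1 tells them to stop the enemas. Section 7.3 tells them that something larger stops. If they take it as the end of that infant's participation, 12.8 gives them no reason to keep recording.

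Sepsis, NEC and diarrhea plausibly delay feeding. Infants lost this way would tend to be late feeders, so their missing feeding times would not be missing at random. The Kaplan–Meier and log-rank analyses in section 14.2 would treat them as if they had the same prospects as infants still under observation. Mean imputation, one of the examples in section 10.3, would give them an average time that is probably too early. If the arms differ in how often triggers occur, the comparison shifts. Time to last meconium is less exposed, because an infant cleared before the trigger keeps that outcome.

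A statistical analysis plan can choose how to handle such gaps, but it cannot restore data that were never collected. That makes this a matter for the protocol.

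**Working it through.** **1. Can 7.3 mean the whole trial?** Compare its five triggers with the outcomes.

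| 7.3 trigger | Counterpart in 8.2 |
|---|---|
| Sepsis | Late-onset sepsis |
| NEC (no stage given) | NEC, stage II or III |
| Diarrhea | Diarrhea |
| Rectal or anal injury | Rectal trauma |
| Positive fecal occult blood | None by name |

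Four of the five have a counterpart among the outcomes, and section 14.4 reports NEC, late-onset sepsis and colorectal and anal injuries as safety events. A trial of 78 + 216 = 294 infants that plans to tabulate these events cannot be meant to close at the first of them. The rule must apply per infant.

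**2. Who is left uncovered?** Under 12.8 follow-up runs to the endpoints unless termination intervenes. An infant whose enemas stop under 7.1 alone, for instance after complete evacuation, is therefore still followed. Only an infant who meets a 7.3 trigger falls under the termination limb, and no passage requires that infant to be followed to full enteral feeding.

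**3. How early would a stop cost the feeding endpoint?** Section 7.2 starts feeds at 24 mL/kg per day and says "feedings will be advanced every 24 hours by 20 mL/kg birthweight per day". The target is 180 mL/kg per day.

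- Requirement: 24 + 20k ≥ 180, so k ≥ 156/20 = 7.8, which means 8 advances.
- Check: 24 + 20 × 7 = 164; 24 + 20 × 8 = 184.

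An infant stopped within 8 days of its first feed cannot yet have met the volume criterion. Section 8.1 words weight gain as an alternative, where 7.2 requires both, so under 8.1 the endpoint might be met sooner.

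**4. Size.** The protocol gives no trigger rates and no feeding times, so there is no figure of its own to reproduce and none can be derived. The following is an illustration in which *every input is assumed*: lognormal feeding time with median 14 days and log-SD 0.3; a trigger adds 8 days; breast milk shortens feeding time directly by 1.5 or 0 days; every trigger falls before full feeding. The stopped infant is censored at a uniform time before its own feeding time, or before the time it would have had without delay; the two rules give the ranges below. There were 1,000,000 simulated infants per arm, with simulation error of about 0.02 days. Entries are breast milk minus saline median, in days.

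| Direct benefit | Trigger rate, breast milk v saline | All followed | Stopped infants censored |
|---|---|---|---|
| 1.5 d | 15% v 25% | -2.38 | -1.64 to -1.84 |
| 1.5 d | 25% v 15% | -0.65 | -1.09 to -1.33 |
| 1.5 d | 20% v 20% | -1.49 | -1.45 to -1.47 |
| 1.5 d | 5% v 7% | -1.64 | -1.53 to -1.56 |
| 0 d | 15% v 25% | -0.87 | -0.15 to -0.36 |
| 0 d | 25% v 15% | +0.88 | +0.15 to +0.37 |

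The difference can be attenuated or exaggerated, and a harm can be understated. With equal rates the shift is at most 0.04 days; with 5% v 7% it is about 0.1 days.

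**The case against.** The strongest reply is that continued follow-up is what the protocol intends. It plans an intention-to-treat analysis. It lists outcomes seen only late. Staff may "check electronic medical records to supplement missing baseline and follow-up data". The steering committee "will also dynamically monitor the rate of follow-up loss". The monthly monitor checks "informed consent, original data, and the absence of data". On that view 7.3 is loosely worded and nobody would stop recording. This stands as evidence of intent, and it is why the harm is put conditionally. It does not remove the defect: none of these passages tells staff to keep following an infant after a 7.3 event, and 7.3 with 12.8 permits the opposite. Section 15 acknowledges that some infants may withdraw before full feeding, and section 11 allows 20% loss. Both show that incomplete observation was expected, but neither addresses a stop that the protocol itself orders.

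Three stronger readings are tempting, and the document does not support them.

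- *That no infant whose enemas are stopped has to be followed.* Section 12.8 covers those stopped under 7.1 alone.
- *That the two trigger lists contradict each other or leave a safety gap.* The criteria in 7.1 are worded as an open list, so extra triggers in 7.3 do not conflict with it. Section 8.2 has no separate list of serious events; it begins "Any adverse events reported: nosocomial infection, nosocomial death, retinopathy of prematurity (ROP, any stage". But 7.1 can be read as the serious ones among those, and colon perforation, absent from 7.3, readily qualifies. Positive occult blood is missing by name from the adverse events in 9.2 ("nosocomial infection, in-hospital death, ROP, CLD, IVH, BPD, LOS, diarrhea, colon perforation, malabsorption, rectal bleeding, and rectal trauma"), yet section 9 says laboratory tests are collected, so it is not shown to go unrecorded. What remains is untidiness worth a cross-reference.
- *That the comparison will be biased by a known amount or in a known direction.* The large shifts in the illustration need an assumed 10-point imbalance in trigger rates.

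**Conclusion.** The point holds for infants who meet a 7.3 trigger. As written, 7.3 says more than 7.1; it cannot mean the whole trial; and read per infant with 12.8 it allows follow-up to end before time to full enteral feeding, hospital days and discharge weight are known. That conflicts with the intention-to-treat analysis and risks informative loss of a co-primary endpoint.

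The consequence depends on three things the protocol does not settle: that staff do stop recording at a trigger, that triggered infants feed later, and that trigger rates differ between arms. If rates are low or similar, the distortion is small. A reader might infer from the wording that the trial's result is unreliable; the document does not support that. It is a correction that should be made, with medium confidence in its practical effect.

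**What to change.** - Reword and retitle 7.3 as discontinuation of enemas in the individual infant.
- Have 7.1 and 7.3 refer to one trigger list, with its content decided by the sponsor's clinicians. If positive occult blood stays on it, name it in 9.2.
- State in both 7.3 and 12.8 that stopping enemas does not stop data collection: every randomised infant with continuing consent is followed for all endpoints to full enteral feeding, discharge or death, and is analysed as randomised.
- If a rule for stopping the whole trial is wanted, write it separately under the data safety monitoring committee.

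The cost is a short amendment and slightly more data collection on infants who are already inpatients and seen daily.
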